### Randomization, blinding, and allocation to interventions

Military bases, regional police forces, and hospital wards were randomly assigned as ‘clusters’ to one of the two intervention groups. A total of 18 clusters were randomized, which were equally divided in 9 clusters that were allocated to the limited intervention and 9 clusters that were allocated to the extensive intervention. In each of these clusters, one or more OPs were assigned to contribute to PerfectFit, based on shown interest. We chose for a cluster design to ensure that the OPs were only active within a single study arm. The organizational unit was the preferred cluster for two reasons. First, OPs from the same organizational unit were all trained to execute the intervention so that discussions among colleagues would not bias the results. Second, grouping participants from the same organizational unit into the same intervention group will prevent so-called “contamination effects” among participants, i.e., talking and sharing experiences about involvement in two different types of interventions, which might influence their behaviors [69, 70].

In the military force we constructed ten clusters consisting of military ground force army bases located in different regions in The Netherlands. Since the police force was facing a large reorganization with possible replacements of OPs from one organizational unit to another, only two clusters could be constructed, based on organizational units in different regions. Randomization in the academic hospital was performed at the ward level, creating a total of 6 clusters.

For all organizations, the OPs only perform work for the health center within that particular organizational unit. Clusters were ordered according to their sizes, i.e. the number of potential eligible participants. For each pair of clusters of similar size within one organization, one of the clusters was randomly allocated to the extensive intervention and the other to the limited intervention. Randomization took place after an OP from the unit had confirmed participation, and prior to the inclusion of individual participants. A researcher who was not otherwise involved in the trial used version 3.0.1 of The R Foundation for Statistical Computing for the randomization. Researchers, participating OPs, and participants were not blinded for the group allocation, since this was impossible given the nature of the intervention and the cluster design.

### Statistical analyses

Demographic and socio-economic characteristics of participants such as age, gender, education, profession, and income level, were collected at the beginning of the study. For the baseline characteristics of Tables 1 and 2, we used descriptive statistics to generate number and percentages for dichotomous and categorical variables, and to generate means and standard deviations of continuous variables. To get insight into the differences between groups, Chi-Square tests and ANOVA-tests were performed.

**Table 1 Tab1:** Baseline characteristics of participants included in the PerfectFit-study according to organization ( *n* = 491)

	Organization 1	Organization 2	Organization 3	P value
	(Police)	(Military)	(Hospital)	
	*n* = 262 (53 %)	*n* = 170 (35 %)	*n* = 59 (12 %)	
Age, mean (sd)	52 (5.8)	49 (4.6)	53 (6.5)	<0.000^*^
Gender:				
Male	201 (82.7 %)	163 (98.2 %)	16 (27.6 %)	<0.000^*^
Educational level				
Low	39 (16.7 %)	16 (9.9 %)	11 (20 %)	<0.000^*^
Medium	147 (63.1 %)	87 (53.7 %)	22 (40 %)	
High	47 (20.2 %)	59 (36.4 %)	22 (40 %)	
Hypertension^a^	78 (31.2 %)	73 (44.5 %)	22 (39.3 %)	0.021^*^
Body Mass Index category				
<25 kg/m2	62 (24.9 %)	34 (20.1 %)	32 (55.2 %)	<0.000^*^
25-30 kg/m2	141 (56.6 %)	101 (59.8 %)	22 (37.9 %)	
>30 kg/m2	46 (18.5 %)	34 (20.1 %)	4 (6.9 %)	
Waist circumference, cm :				
High (female >88 cm; male >102 cm)	100 (41.3 %)	71 (43.0 %)	30 (52.6 %)	0.299
Obesity^b^	104 (43.5 %)	75 (45.5 %)	30 (52.6 %)	0.462
Family history of CVD^c^	97 (37.6)	61 (39.4)	24 (42.9)	0.754
Diabetes mellitus (DM) type II^d^	10 (4.0)	3 (1.9)	1 (1.8)	0.408
Dyslipidemia^e^	238 (92.6 %)	154 (91.7 %)	56 (94.9 %)	0.715
Health risk behavior:				
Lack of physical activity	107 (42.0)	42 (26.9)	20 (37.0)	0.009^*^
Smoking	42 (16.5)	27 (16.9)	3 (5.4)	0.088
Framingham 10-year CVD risk score category^f^				
Low (<10 %)	153 (66.5 %)	120 (78.9 %)	32 (58.2 %)	0.003^*^
Intermediate (≥10 %, <20 %)	68 (29.6 %)	22 (14.5 %)	20 (36.4 %)	
High (≥20 %)	9 (3.9 %)	10 (6.6 %)	3 (5.5 %)	
Number of inclusion criteria:				
1	51 (19.8 %)	26 (15.4 %)	7 (11.9 %)	0.235
2	68 (26.5 %)	62 (36.7 %)	21 (35.6 %)	
3	77 (30.0 %)	43 (25.4 %)	20 (33.9 %)	
≥4	61 (23.7 %)	38 (22.5 %)	11 (18.6 %)	

^*^statistically different, continuous measurements based on ANOVA test and categorical measurements based on Chi-Square test

^**a**^Hypertension is defined as diastolic blood pressure higher than 90 mmHG or systolic blood pressure higher than 140mmHG or taking antihypertensive drugs

^**b**^Obesity is defined as BMI >30 kg/m^2^ or waist circumference >88 cm for females or >102 cm for males

^**c**^Family history of CVD is defined as a first degree family member who suffered a CVD at any age

^**d**^Diabetes is defined as having a sober blood glucose higher than 6.1 or self-reported diagnosis of diagnosis

^**e**^Dyslipidemia is defined as having increased levels of at least one type of lipids in the blood (total cholesterol ≥ 5 mmol/l, or LDL cholesterol ≥ 2.5 mmol/l; or triglycerides: ≥ 1.7,mmol/l, or HDL cholesterol: ≤ 1.0 mmol/l)

^**f**^EuroSCORE and QRISK2 will be calculated after completion of the intervention, at 12 months

**Table 2 Tab2:** Baseline characteristics of the study population (demographics, health and work-related factors) in two intervention arms

	Limited Intervention	Extensive Intervention	P value
	*n* = 218	*n* = 275	
Age, mean (sd)	52.1 (6.0)	50.7 (5.4)	<0.006^*^
Organization			0.007
Police	124 (57.1)	138 (50.4)	
Military	60 (27.6)	110 (40.1)	
Hospital	33 (15.2)	26 (9.5)	
Gender:			
Male	154 (77.0 %)	226 (84.6 %)	0.036^*^
Educational level			0.011^*^
Low	33 (17.5 %)	33 (12.6 %)	
Medium	116 (61.4 %)	140 (53.6 %)	
High	40 (21.2 %)	88 (33.7 %)	
Hypertension^a^	73 (35.1 %)	100 (38.2 %)	0.493
Body Mass Index category			
<25 kg/m2	64 (29.9 %)	64 (24.4 %)	0.294
25-30 kg/m2	117 (54.7 %)	147 (56.1 %)	
>30 kg/m2	33 (15.4 %)	51 (19.5 %)	
Waist circumference, cm :			
High (female >88 cm; male >102 cm)	79 (39.7 %)	122 (46.0 %)	0.173
Obesity^b^	81 (40.7 %)	128 (48.9 %)	0.082
Family history of CVD^c^	78 (38.0 %)	104 (39.4 %)	0.767
Diabetes mellitus (DM) type II^d^	8 (3.9 %)	6 (2.3 %)	0.314
Dyslipidemia^e^	197 (91.6 %)	251 (93.3 %)	0.484
Health risk behavior:			
Lack of physical activity	73 (35.6 %)	96 (36.9 %)	0.770
Smoking	23 (11.1 %)	49 (18.6 %)	0.026^*^
Framingham 10-year CVD risk score category^f^			
Low (<10 %)	123 (66.5 %)	182 (72.2 %)	0.430
Intermediate (≥10 %, <20 %)	52 (28.1 %)	58 (23 %)	
High (≥20 %)	10 (5.4 %)	12 (4.8 %)	
Number of inclusion criteria:			
1	43 (20.3 %)	41 (15.0 %)	0.323
2	64 (30.2 %)	87 (31.9 %)	
3	63 (29.7 %)	77 (28.2 %)	
≥4	42 (19.8 %)	68 (24.9 %)	

^*^statistically different, continuous measurements based on ANOVA test, categorical measurements based on Chi-Square test

^**a**^Hypertension is defined as diastolic blood pressure higher than 90 mmHG or systolic blood pressure higher than 140mmHG or taking antihypertensive drugs

^**b**^Obesity is defined as BMI >30 kg/m^2^ or waist circumference >88 cm for females or >102 cm for males

^**c**^Family history of CVD is defined as a first degree family member who suffered a CVD at any age

^**d**^Diabetes is defined as having a sober blood glucose higher than 6.1 or self-reported diagnosis of diagnosis

^**e**^Dyslipidemia is defined as having increased levels of at least one type of lipids in the blood (total cholesterol ≥ 5 mmol/l, or LDL cholesterol ≥ 2.5 mmol/l; or triglycerides: ≥ 1.7,mmol/l, or HDL cholesterol: ≤ 1.0 mmol/l)

^**f**^EuroSCORE and QRISK2 will be calculated after completion of the intervention, at 12 months

Future analyses will be performed according to the Intention-to-treat principle [71]. Repeated measurements with mixed models techniques will be used to compare the primary outcome (general health scores) between the extensive and limited intervention groups, adjusted for potential confounders such as socioeconomic determinants (including employment status, profession, income level, education), and taking into account the cluster randomization (multilevel analysis). A cost analysis will be performed to determine the costs of the extensive health intervention compared to the limited health intervention, including the change in health care consumption.

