### Outcome measures

The following outcome measures will be taken into account:**Primary outcome measure:**

General health

At baseline, 6 months and 12 months, we measure (d) general health using the first question of the Short Form 36 Health Survey (SF-36) [48] (‘Overall, how would you rate your health?’), which has five possible answers, ranging from ‘poor’ to ‘excellent’.**Secondary outcome measures:**

Quality of life

Quality of life and its utility values will be calculated using the EuroQol 5 dimensions self-report questionnaire (EQ-5D) [49] and two domains from the SF-36 (physical functioning and vitality) [48]. The EQ-5D is a health status classification system consisting of five dimensions: mobility, self-care, usual activities, pain/discomfort, and anxiety/depression. We distinguish three levels for each dimension: no problems, moderate problems, and extreme problems. Within the SF-36, 4 questions are asked for physical functioning with 5 answering options, ranging from “totally agree” to “totally disagree”. For vitality 4 questions are asked with 6 answering options ranging from “all the time” to “never”.

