### Sample size and power calculation

The primary outcome measure in this study is general health. Based on a study of more than 4000 asymptomatic Dutch individuals [67], we assumed that the average value for general health score measured by the SF-36 within our target study population is 71 (SD 19, scale 0–100). Based on an intervention study that assessed general health, albeit with a less intensive intervention [68], we assume a relevant difference in the general health score between the intervention and control groups after 12 months of 10 % in favor of the intervention group. With a power of 80 %, a significance level of 5 %, two-tailed testing, a compensation for cluster randomization with an estimated intra-cluster correlation coefficient of 0.05, the assumption of similar groups, and with the intention of demonstrating superiority, approximately 220 participants per group are needed to demonstrate a difference in treatment effect of 10 % between the two groups. With an expected participation of 50 % (based on previous studies of health interventions for military personnel) and a loss to follow-up of 30 %, the RCT required inviting 2 × 634 individuals, so 1268 in total.

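### The primary model does not name organisation, the factor within which clusters were randomised, and the text on baseline balance disagrees with Table 2

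*Protocol article*

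**What the plan says.** Under Randomization, blinding, and allocation to interventions, the article describes 18 clusters: ten military, two police and six hospital. They were ordered by size and allocated as follows: "For each pair of clusters of similar size within one organization, one of the clusters was randomly allocated to the extensive intervention". Its partner went to the limited arm.

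Under Statistical analyses, general health is to be compared by mixed models for repeated measurements, "adjusted for potential confounders such as socioeconomic determinants (including employment status, profession, income level, education), and taking into account the cluster randomization". The examples are introduced by a phrase that leaves the list open. Neither organisation nor pair is named.

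Under Outcome measures, the primary outcome has three occasions: "At baseline, 6 months and 12 months, we measure (d) general health".

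Two statements bear on how much adjustment is expected. The Results say that randomisation produced similar groups and that smoking was the only difference found. The Discussion infers from the balance of health factors that little adjustment will be needed. Table 2 marks age, gender, education and smoking as different, and also prints p = 0.007 for organisation.

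**The concern.** When randomisation is restricted within a factor, the analysis should normally condition on that factor. Here it is organisation, and Table 1 shows that the three organisations differ in age, sex, education, hypertension, BMI category, physical activity and Framingham category. All of these could plausibly go with self-rated health.

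Two things follow if the fitted model leaves organisation out. Differences in mean health between police, military and hospital staff are read as variation between clusters, so the reported standard error is larger than it needs to be. And because the organisation mix differs by arm, part of any such difference moves into the treatment estimate. The remarks that only smoking differed and that little adjustment is needed make the omission more likely, and they conflict with the article's own table.

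**Working it through.** **1. The target difference.** The sample size section assumes a mean of 71 and SD of 19, a difference "after 12 months of 10 % in favor of the intervention group", and an "estimated intra-cluster correlation coefficient of 0.05". Read as relative, 10% of 71 is 7.1 points. Per group: 2 × (1.960 + 0.842)² × 19² / 7.1² = 112.4. The cluster size is not stated. With an assumed 20 per cluster the design effect is 1 + 19 × 0.05 = 1.95, and 112.4 × 1.95 = 219.2, which matches "approximately 220 participants per group are needed". An absolute difference of 10 points would need an assumed cluster size of about 58, so 7.1 is used below.

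**2. The organisation imbalance.** Table 2 gives these counts (limited, extensive): police 124, 138; military 60, 110; hospital 33, 26. The totals are 217 and 274. Expected counts in the limited arm are 262 × 217/491 = 115.8, 170 × 217/491 = 75.1 and 59 × 217/491 = 26.1. Chi-square over the six cells is 9.80 on 2 df, p = 0.0074, which reproduces the printed 0.007.

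**3. Text against table.** Table 2 prints p below 0.05 for five characteristics, whereas the Results name only the last:
- organisation 0.007
- age <0.006
- gender 0.036
- education 0.011
- smoking 0.026

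**4. Shift in the estimate.** The difference in military share is 110/274 − 60/217 = 0.401 − 0.276 = 0.125. If military staff score d points above the other two organisations (assumption; the article gives no general health score by organisation), the crude contrast shifts by 0.125 × d:
- d = 5: 0.62 points, or 0.62/7.1 = 9% of the target
- d = 10: 1.25 points, or 1.25/7.1 = 18% of the target

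**5. Effect on the standard error.** A random-intercept model was simulated with 17 clusters, 30% loss, SD 19 and 3,000 runs per setting. Assumptions: equal cluster sizes within organisation and arm, and the lost military cluster in the limited arm. Setting A puts the military 5 points above police and hospital. Setting B also puts the hospital 5 points below the police.

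| ICC, setting | Organisation omitted: shift; mean SE (true SD) | Organisation included: shift; mean SE (true SD) |
|---|---|---|
| 0.01, A | 0.67; 2.88 (2.63) | −0.03; 2.55 (2.64) |
| 0.01, B | 1.13; 3.18 (2.70) | −0.01; 2.55 (2.66) |
| 0.05, A | 0.66; 3.44 (3.27) | 0.03; 3.15 (3.35) |
| 0.05, B | 1.11; 3.79 (3.33) | 0.03; 3.17 (3.36) |

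Without organisation the reported SE exceeds the true SD, and it is 9% (3.44/3.15) to 25% (3.18/2.55) larger than with organisation. Including organisation removes the shift.

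**6. Degrees of freedom.** One military cluster was lost after randomisation, which leaves 17. With an intercept, treatment and two organisation terms, 17 − 4 = 13. A critical value of 1.96 then has true level P(|t₁₃| > 1.96) = 0.072. In the simulation with organisation included, the large-sample test rejected a true null in 7.1 to 9.5% of runs, and t on 13 df in 4.9 to 7.0%. With organisation omitted and organisation differences present, the large-sample test rejected in 4.8 to 6.4%.

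**7. Organisation or pair.** The design had 5 + 1 + 3 = 9 pairs. The lost military cluster leaves eight intact. Pair effects would leave 17 − 9 − 1 = 7 df, and the cluster without a partner would contribute nothing to the treatment contrast. Organisation effects leave 13.

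**The case against.** The strongest reply is that nothing needed is ruled out. The covariate list gives examples, so organisation may well be in the full plan. Profession is on the list and could carry much of the contrast between soldiers, police officers and hospital staff. This stands, in that the article does not exclude organisation. It does not settle the matter: the coding of profession is not given, and only an organisation term ensures that the comparison is made within the groups that were randomised.

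A reader might go further and infer that baseline general health is discarded, that clustering is handled badly, and that the test is anti-conservative. The documents do not support this. Baseline is one of three occasions of a repeated-measures outcome and enters such a model naturally; the article just does not say how. Clustering is modelled explicitly. No large-sample test is stated, and the choice of degrees of freedom may properly be left to an analysis plan. The two effects on the error bars also run in opposite directions: omitting organisation tends to widen intervals, while a large-sample test on 17 clusters narrows them.

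The shift is also modest. It rests on an assumed score difference, applies to a contrast without profession or baseline in the model, and is small beside a standard error of roughly 2.5 to 3.8 points.

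Finally, having only one police cluster per arm is a constraint that the article discloses and explains. Analysis wording cannot remove it.

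**Conclusion.** The point holds as a nearly free improvement; it is not a defect that invalidates the analysis. Randomisation was restricted within organisation, the arms differ in organisation mix, and the primary model does not name organisation. The remarks on balance contradict Table 2 and should be corrected whatever model is used.

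The firm figures are the 12.5 percentage-point gap in military share and its p value of 0.007. That p value treats individuals as independent, so the case for the term rests on the randomisation scheme more than on the test. The shift of 0.6 to 1.2 points and the standard error that is 9 to 25% too wide depend on assumed differences of 5 to 10 points and 5 points respectively. If the organisations do not differ in general health, both vanish. The 7% error rate would arise only if organisation were added and a large-sample test used. That is a reason to choose the degrees of freedom together with the organisation term, and it is not a fault of the stated plan.

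**What to change.** State the primary model as a mixed model for general health at baseline, 6 and 12 months with:
- organisation, the randomisation stratum, as a fixed effect;
- a random intercept for cluster, as already implied by the multilevel analysis;
- baseline as one of the occasions, with a mean common to both arms, which retains those of the 16 participants without a baseline questionnaire who give follow-up data;
- a small-sample degrees-of-freedom method such as Kenward-Roger or Satterthwaite. Fixed 13 df was still slightly liberal at ICC 0.05 in the simulation.

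Do not offer matched-pair effects as an equivalent alternative, given the broken pair. A sensitivity analysis without the police pair is optional; it would drop 262 of 491 participants and leave 229.

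Correct the Results statement that only smoking differed and the Discussion statement that little adjustment is needed, so that both agree with Table 2.

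The cost is wording and two degrees of freedom. No new data are needed: organisation is tabulated for 491 of the 493 participants, whereas education, already on the covariate list, is missing for 40.

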### Economic evaluation

An economic evaluation will be performed, according to the Dutch guidelines for cost-effectiveness analyses, to evaluate the trade-off between costs and benefits. Analyses will be performed both from the perspective of the organization and from a societal perspective. In this study we will consider direct and induced costs of the intervention. The timeframe of the analyses is 12 months and we will use a model for extrapolation to long-term results. The cost-benefit analysis performed from the organizational perspective will include the differences in employability (in monetary units) and the additional organizational costs for applying the elements from the extensive intervention in addition to the limited intervention. A secondary analysis will be performed in which we will simulate a no-HRA-scenario and calculate the costs and benefits without either one of our interventions as reference. In the cost-effectiveness analyses from a societal perspective, effectiveness will be expressed using QALY’s, whereas costs will be expressed as total healthcare costs (direct plus induced costs) and societal costs. Direct healthcare costs consist of costs of the intervention programs and costs for adapting the intervention for the target groups (including construction and use of the web-portal and MI-training of OPs). Induced healthcare costs consist of healthcare consumption (outpatient visits, diagnostic and therapeutic procedures, medication, and hospital admissions). Societal costs consist of costs of employee absence in order to participate in the intervention, absenteeism, productivity at work, individual costs for undertaking health promotion activities (including contribution fees to a sports centre and time costs), and any additional travel costs and parking expenses.

## Results

### Baseline characteristics of participants

Figure 1 shows the CONSORT diagram [72] of the flow of clusters and participants through the first phases of the trial. In total, 9 clusters (*n* = 217), were assigned to the limited intervention (control), and 9 clusters (*n* = 274) to the extensive intervention (intervention). One cluster dropped out after randomization and before any cardio screenings were done, because the only OP within this cluster had other priorities in work. Three more OPs dropped out before any cardio screenings were done, two because of personal problems and one because she left her job. A total of 652 employees undertook the cardio screening. Based on these cardio screenings, 91.4 % (*n* = 598) were found to have risk factors for CVD, of whom 82.3 % were included (*n* = 493). Reasons for no inclusion were the presence of exclusion criteria or retirement or having to go abroad for work in the near future. For 16 participants the baseline questionnaire was missing, but we did receive blood- or anthropometric-measurements. The number of missings ranged from *n* = 1 (for the variable age) to *n* = 40 (for the variable level of education).

Baseline characteristics of participants in the three organizations are presented in Table 1. The military and police forces included a majority of males, whereas the hospital included mostly females. Among participants of the police force more than 76 % had a BMI higher than 25 kg/m2, and in the military force this percentage was 80.5 %. The percentage in the hospital of 46 % is lower and is similar to the average for the Dutch population.

Table 2 presents the baseline characteristics of the extensive intervention versus control study groups. The average age of the participants was 52, and 81.4 % were male. The randomization was successful in creating study groups with similar characteristics. Only for smoking a difference between the groups was found (*p* = 0.026). The CVD risk based on the Framingham score showed that more than 30 % of our study population is at intermediate or high risk, without differences in distribution between the two groups (*p* = 0.430).

